### Statistical Analysis

The sample size was calculated in reference to collected data on the management of choledocholithiasis in the trial center Vilnius University Hospital Santaros Klinikos [11]. In our previous study, the mean treatment durations for different management strategy groups (LC-IOC first and ERCP first) were 5.37 and 7.13 days, with SDs of 2.5 and 2.8, respectively, and these findings were used to calculate the requested sample size. The program G*Power version 3.1.9.2 was used for calculations. It was calculated for a two-tailed *t* test for means of two independent groups. The significance level was selected to be .05, with a power of 0.8. The required sample size is 74 (37 valid participants in each of the two groups).

The endpoints in different management groups will be analyzed using the chi-square test or *t* test for independent means. Two-sided hypotheses are to be checked, and a *P* value <.05 will be considered statistically significant. If the distribution is nonnormal, a transformation, such as the logarithm or square root function, can be applied to obtain a normal distribution or nonparametric tests, such as the Mann-Whitney test, can be used. To evaluate the achieved power, a post-hoc power analysis calculation will be performed.
As for the primary outcome, a difference of 2 days of hospital stay will be considered clinically meaningful.

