### Randomization and Data Protection

Eligible patients who provide informed consent will be assigned to the groups “endoscopy first” or “cholecystectomy first” randomly, according to a premade sequence. The sequence is generated by a randomization website [15]. The sequence is created using block randomization of two elements A and B (“endoscopy first” and “cholecystectomy first”) in a ratio of 1:1. According to the sequence, sheets with group names are enclosed in opaque envelopes. Envelopes are numbered, and the envelope number is the patient number in the trial. When a new participant is enrolled, the topmost envelope is opened by one of the investigators and the participant is randomized into the specified group.

All collected data are coded, that is, every case receives an individual number. Only coded data will be employed for statistical analysis and publishing. Uncoded data are available only for researchers of the trial and, on special and reasonable request, for the coordination center for biomedical research of the institution and Biomedical Research Ethics Committee.

Data are processed and stored in an electronic database, and physical (“paper”) copies are stored at the trial center in accordance with procedures established by law.

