### Outcomes

The primary endpoint is the length of hospital stay (duration from enrollment into the trial to discharge, in days).

The secondary endpoints are as follows:

1. Diagnostic accuracy of the different management strategies (proportion of correctly diagnosed [true positive and true negative] cases in the entire sample; time frame: 6 to 12 months).

2. Technical success of diagnostic and therapeutic biliary procedures (IOC, EUS, ERCP) (during the active treatment period). For IOC, successful cannulation and contrast media injection into the CBD are considered. For EUS, successful visualization of the CBD is considered. For ERCP, successful cannulation and contrast media injection into the CBD are considered. Successful CBD clearance is also considered.

3. Postoperative course and possible complications of treatment (time frame: up to 1 month). With regard to adverse events of endoscopic interventions and IOC, we consider (1) bleeding, hematemesis and/or melena, or hemoglobin drop >20 g/L; (2) perforation, evidence of air or luminal contents outside the gastrointestinal tract; (3) post-ERCP pancreatitis, new or worsening abdominal pain persisting for at least 24 h and requiring analgesics after ERCP in conjunction with an elevation in serum amylase or lipase levels greater than three times the normal upper limit [16,17]. We also consider assessment of the postoperative course by the Clavien-Dindo classification of surgical complications [18].

4. Cost of treatment (charges for diagnostic procedures, invasive procedures, surgery, and antibacterial treatment, if needed, as well as hospital charges).

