First, it is essential to define the criteria for different risk groups. While the majority of recent trials evaluating the accuracy of choledocholithiasis prediction refer to ASGE guidelines, we performed an analysis of seven different studies on this prognostic system, and the predictive values of high-risk criteria were quite mediocre. The general sensitivity was 52.4%, specificity was 60.8%, positive-predictive value was 65.6%, negative-predictive value was 47.4%, and accuracy was 55.9% [11]. At the center of this trial, an original prognostic index (VUHI) has been used for the prediction of choledocholithiasis risk before LC since 1999. It is calculated by the following formula: VUHI = A / 30 + 0.4 × B, where A is the total bilirubin concentration (µmol/L) and B is the CBD diameter measured by ultrasound. The results of our previous study showed that the VUHI had comparable and, for some parameters, superior performance than the prognostic system of the ASGE guidelines [11]. The most modest measure was the specificity of VUHI (54%), while the sensitivity was 80.5%. This implied that earlier threshold of the index was kind of a weak spot in the evaluation system. The newly generated model for predicted probability of choledocholithiasis sets limits for the intermediate risk group, that is, it determines which patients should undergo additional noninterventional investigation. We chose thresholds for the intermediate risk group of 25% and 75% of the probability for CBD stones considering that the upper limit of 50% in the ASGE guidelines would still leave a certain number of patients for unnecessary ERCP. Latest European Association for the Study of the Liver (EASL) guidelines also state that patients with intermediate probability should undergo further evaluation with EUS or MRCP, but do not define what this intermediate probability is [20]. Meta-analyses showed that these two diagnostic procedures are quite comparable, but EUS has better diagnostic accuracy [21,22]. Just one trial comparing EUS and IOC was found in the PubMed database, and it showed better predictive values of IOC [23]. Considering that this study was performed 20 years ago and imaging technologies have advanced since then, it is worth comparing these two methods again. When comparing IOC with ERCP as a diagnostic procedure, a systematic review of 10 trials by Gurusamy et al showed slightly higher sensitivity for IOC with no difference in specificity [24].

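### The primary analysis of hospital stay may move, without a stated rule, from a t test on days to tests that do not estimate the difference in mean days

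*Protocol article*

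**What the plan says.** In the Protocol article, Outcomes, the primary endpoint is "length of hospital stay (duration from enrollment into the trial to discharge, in days". Under Statistical Analysis the sample size comes from a two-tailed t test on mean stays that "were 5.37 and 7.13 days, with SDs of 2.5 and 2.8, respectively". The settings are: "The significance level was selected to be .05, with a power of 0.8". The same section calls a difference of 2 days clinically meaningful, and the Discussion repeats 2 days as the minimal important difference.

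The analysis rule begins: "The endpoints in different management groups will be analyzed using the chi-square test or" a t test for independent means. It continues: "If the distribution is nonnormal, a transformation, such as the logarithm or square root function, can be applied", or nonparametric tests such as Mann-Whitney may be used instead. Both routes are permissive and open-ended, since each is introduced by an example. The primary endpoint has no rule of its own, and no covariate is named. Randomization is in blocks, "in a ratio of 1:1", with no stratification factor stated.

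The Discussion defines VUHI as total bilirubin divided by 30 plus 0.4 times duct diameter: "where A is the total bilirubin concentration (µmol/L) and B is the CBD diameter measured by ultrasound". Both components are needed to establish eligibility, so VUHI is known for every patient before allocation.

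**The concern.** The t test on days, the sample size and the 2-day criterion all concern the same quantity, the difference in mean days. A t test on logs compares geometric means, a t test on square roots compares means of root-days, and Mann-Whitney compares the probability that a patient in one arm stays longer than a patient in the other. When the two distributions differ in spread or shape, these can differ between arms while the mean stays are equal.

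Different spreads are plausible in this design. By the Procedure section, a cholecystectomy-first patient without stones is finished at surgery, while one with stones usually waits for a postoperative ERCP. An endoscopy-first patient has any ERCP under the same anaesthesia as the EUS, with surgery still to come. The planning SDs do not settle the question, because they come from LC-IOC-first and ERCP-first groups and not from an EUS-first group.

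At stake is what a significant primary result would mean. It might not support a claim about mean days, and it could not be set directly against the 2-day criterion.

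**Working it through.** **1. The plan's own figure.** Inputs from Statistical Analysis: means 5.37 and 7.13, SDs 2.5 and 2.8, alpha .05, power 0.8, two-sided ("Two-sided hypotheses are to be checked").

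- Difference = 7.13 − 5.37 = 1.76 days.
- Pooled SD = √((2.5² + 2.8²)/2) = √7.045 = 2.654.
- Standardized difference d = 1.76/2.654 = 0.663.
- The noncentral t calculation gives 36.69, so 37 per arm and 74 in total.

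The stated 74 reproduces, and it belongs to a t test on raw days. Power for 1.76 days is 80.3% at 37 per arm and 92.2% at 53 per arm (the 106 of the Abstract).

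**2. Would the alternatives be used?** The article gives neither a distribution nor a criterion for nonnormality, so both are assumed here: lognormal stays rounded to whole days, and Shapiro-Wilk p < .05 in either arm. With mean 6.25 (= (5.37 + 7.13)/2) and SD 2.65, the trigger fires in 96% of simulated trials at 37 per arm and in over 99% at 53. At the planning means and SDs with 37 per arm, the four tests disagree about significance in 11% of trials.

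**3. What the other scales compare.** For a lognormal, geometric mean = mean/√(1 + (SD/mean)²). With both means 6.25:

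- SD 2.5: 6.25/√1.16 = 5.80 days.
- SD 5: 6.25/√1.64 = 4.88 days.

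The mean stays are equal, yet a log-scale test has a real difference to find.

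**4. Rejection rates with equal means of 6.25 days and SDs 2.5 and 5** (assumed; the contrast is deliberately large):

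| Test | 37 per arm | 53 per arm |
|---|---|---|
| t or Welch on days | 6% | 6% |
| t on square roots | 12–13% | 14% |
| t on logs | 25% | 34% |
| Mann-Whitney | 23–24% | 32% |

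The rates off the day scale rise with sample size because those tests are detecting a true difference in another quantity.

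**5. Identical distributions in both arms** (assumed lognormal, mean 6.25):

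| Procedure | SD 2.65, 37 / 53 per arm | SD 5, 37 / 53 per arm |
|---|---|---|
| Any one test, fixed in advance | 4.6–4.9% | 4.6–5.1% |
| Mann-Whitney if Shapiro-Wilk p < .05, else t | 4.7 / 4.9% | 4.7 / 5.1% |
| Smallest p value of the four | 6.6 / 6.8% | 7.1 / 7.8% |

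**6. Covariate adjustment.** If VUHI explains a share R² of the variance, the standardized difference becomes d/√(1 − R²). The documents give no R², so a range is assumed:

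| R² | Power, 37 per arm | Power, 53 per arm |
|---|---|---|
| 0 | 80% | 92% |
| 2% | 81% | 93% |
| 10% | 84% | 95% |
| 20% | 88% | 97% |

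In simulation with no group difference, regression with robust standard errors rejected in 4.2–4.5% at 37 and 53 per arm.

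**The case against.** The strongest reply is that the article does fix a default, a significance level and a fallback conditional on the distribution, and that the normality criterion and the order of the fallbacks belong in an analysis plan that is not shown. That stands for the missing criterion. It does not cover the permission itself: the text allows a choice among analyses that target different quantities, for the endpoint that carries the superiority claim.

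A reader might infer that the plan inflates type I error to 6–8%. The documents do not support that. The figure describes an analyst who runs all four tests and keeps the smallest p value, whereas the written switch depends on the distribution and not on significance. A fixed fallback rule stays near 5%, so 6–8% is an upper bound under assumed shapes.

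A reader might also call the unadjusted comparison an error. It is not: the arms are randomized with no stated stratification factors, so an unadjusted test is valid. Nothing in the documents links VUHI to length of stay, and eligibility restricts it to 2.6–6.9, which may limit what it explains.

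Nor is 2 days a test margin. It is a statement of clinical relevance, and a mean difference in days could be reported beside any test. The plan does not say that it would be.

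Extending the point to cost is not supported either. Cost is a secondary endpoint, and the details of its analysis are properly left to an analysis plan.

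Finally, log and rank tests can have more power with skewed stays: at the planning means and SDs with 37 per arm, 89% and 86% against 80% for the t test under the assumed lognormal. That is a fair reason to choose one in advance, with its own effect measure and its own relevance threshold. It is not a reason to leave the choice open.

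**Conclusion.** The point holds as one about what the primary analysis estimates. As written, the analysis can leave mean days once the distribution has been seen, without a rule, while the sample size and the relevance criterion remain in days. A significant log or rank result would then not establish a difference in mean stay.

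The size depends on how far the spreads differ, which is unknown. The 23–34% for log-t and Mann-Whitney rests on assumed lognormal stays with one SD twice the other. At the planning SDs of 2.5 and 2.8 with equal means of 6.25, the geometric means would be 5.80 and 6.25/√(1 + (2.8/6.25)²) = 5.70 days, so the effect would be small. The error-rate side is modest and avoidable. The day-scale test needs no rescue from nonnormality at these sample sizes under the shapes tried: it stayed near 5% with equal spreads and near 6% with strongly unequal ones.

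**What to change.** Before any comparison by arm, name one primary analysis: the difference in mean hospital days with a 95% CI, from linear regression of days on allocated arm with continuous VUHI as covariate and small-sample heteroscedasticity-robust (HC3) standard errors. If an unadjusted analysis is preferred, name Welch's t test with its CI. List Mann-Whitney and the transformed t tests as sensitivity analyses that do not replace the primary result, and read the 2-day criterion against the estimated difference in mean days and its interval.

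The cost is a few sentences in the analysis plan. The sample size of 74 is unaffected, and VUHI is already recorded for eligibility. The article reports 66 of 106 patients enrolled as of June 2020, so at that date the choice could still be fixed before the final data were in hand.

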### Outcomes

The primary endpoint is the length of hospital stay (duration from enrollment into the trial to discharge, in days).

The secondary endpoints are as follows:

1. Diagnostic accuracy of the different management strategies (proportion of correctly diagnosed [true positive and true negative] cases in the entire sample; time frame: 6 to 12 months).

2. Technical success of diagnostic and therapeutic biliary procedures (IOC, EUS, ERCP) (during the active treatment period). For IOC, successful cannulation and contrast media injection into the CBD are considered. For EUS, successful visualization of the CBD is considered. For ERCP, successful cannulation and contrast media injection into the CBD are considered. Successful CBD clearance is also considered.

3. Postoperative course and possible complications of treatment (time frame: up to 1 month). With regard to adverse events of endoscopic interventions and IOC, we consider (1) bleeding, hematemesis and/or melena, or hemoglobin drop >20 g/L; (2) perforation, evidence of air or luminal contents outside the gastrointestinal tract; (3) post-ERCP pancreatitis, new or worsening abdominal pain persisting for at least 24 h and requiring analgesics after ERCP in conjunction with an elevation in serum amylase or lipase levels greater than three times the normal upper limit [16,17]. We also consider assessment of the postoperative course by the Clavien-Dindo classification of surgical complications [18].

4. Cost of treatment (charges for diagnostic procedures, invasive procedures, surgery, and antibacterial treatment, if needed, as well as hospital charges).

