**Methods:**

This is a randomized, active-controlled, single-center clinical trial enrolling adult patients undergoing laparoscopic cholecystectomy for symptomatic gallbladder stones with intermediate risk of choledocholithiasis. The risk of choledocholithiasis is calculated using an original prognostic score (the Vilnius University Hospital Index). This index in a retrospective evaluation showed better prognostic performance than the score proposed by the American Society for Gastrointestinal Endoscopy in 2010. A total of 106 participants will be included and randomized into two groups. Evaluation of bile ducts using endoscopic ultrasound and endoscopic retrograde cholangiography on demand will be performed before laparoscopic cholecystectomy for one arm (“endoscopy first”). Intraoperative cholangiography during laparoscopic cholecystectomy and postoperative endoscopic retrograde cholangiopancreatography on demand will be performed in another arm (“cholecystectomy first”). Postoperative follow-up is 6 months. The primary endpoint is the length of hospital stay. The secondary endpoints are accuracy of the different management strategies, adverse events of the interventions, duct clearance and technical success of the interventions (intraoperative cholangiography, endoscopic ultrasound, and endoscopic retrograde cholangiography), and cost of treatment.

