## Introduction

Gallbladder stones can be silent or symptomatic. This statement is also valid when speaking about choledocholithiasis, which involves stones situated in the common bile duct (CBD). About 10% to 18% of people undergoing cholecystectomy for gallstones have concomitant CBD stones [1]. Untreated choledocholithiasis can lead to acute biliary pancreatitis, acute ascending cholangitis, and secondary sclerosing cholangitis; thus, it is essential to diagnose and treat it on time. Endoscopic retrograde cholangiopancreatography (ERCP) became a prominent diagnostic method for CBD stones since its introduction to clinical practice in the 1970s [2]. Later on, it was agreed that use of ERCP for diagnostic reasons should be minimized and that it should not be used for first-line diagnostics as it carries a considerable risk (5% to 10%) of postprocedural complications [3]. It has been noticed that adverse events occur more often in patients with low risk of choledocholithiasis [4]. The possibility to avoid using ERCP for diagnostic purposes came with the introduction of new less invasive diagnostic procedures, such as magnetic resonance cholangiopancreatography (MRCP), endoscopic ultrasound (EUS), and intraoperative cholangiography (IOC) during cholecystectomy. Therefore, in the 2000s, a discussion about more careful patient selection for ERCP began, as it should be considered only in those with high probability of demand for therapeutic interventions (ie, stone removal), and patients with intermediate risk for choledocholithiasis should undergo additional investigation.

The most frequently used system to evaluate the risk of choledocholithiasis was proposed in 2010 by the American Society for Gastrointestinal Endoscopy (ASGE) [5]. It already stratifies the probability of CBD stones into low, intermediate, and high risk groups, and it suggests noninvasive investigations for the intermediate risk group, although its predictive value is not completely satisfying [6-10]. These results encourage the development of more accurate prognostic systems.

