### Procedure

The participants of the trial will undergo CBD evaluation depending on the group assignment. For the group “endoscopy first,” EUS is used to evaluate bile ducts. If stones are seen in the extrahepatic bile ducts, ERCP and CBD stone removal are performed during the same general endotracheal anesthesia. LC is performed after endoscopic procedures as soon as possible. In the group “cholecystectomy first,” LC with IOC is performed. If stones are found, postoperative ERCP with CBD stone removal is applied (during cholecystectomy if the CBD is completely blocked or as soon as possible).

EUS is performed with linear or radial Olympus ultrasound endoscopes. The CBD, pancreatic head, and adjacent structures are visualized from the duodenal bulb and descending duodenum. EUS is considered positive for a CBD stone when a constant hyperechogenic lesion with acoustic shadowing is seen in CBD projection.

ERCP procedures are performed by experienced endoscopists (each has more than 5 years of experience in ERCP and has done more than 500 procedures). Olympus side-viewing endoscopes (TJF-160VR) are used. Primary deep selective cannulation of the CBD is performed with a sphincterotome or cannula and guidewire technique. Diatrizoate (Urografin, Bayer) and iohexol (Omnipaque, GE Healthcare) are used as contrast media. Endoscopic sphincterotomy is performed over a guidewire technique with an Olympus pull-type sphincterotome. Papillary balloon dilation using a through-the-scope balloon catheter is applied when a stricture is indicated. Stones are removed using a retrieval balloon catheter and/or a Dormia basket. Complete clearance of the CBD is documented with a balloon catheter cholangiogram at the end of the procedure. ERCP is considered positive when a filling defect is seen in the cholangiogram and/or a stone is evacuated from the CBD. ERCP is considered unsuccessful when cannulation of bile ducts is technically impossible.

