### Follow-Up

Participants are followed as treated inpatients after LC (short-term surveillance) and for 6 months after hospitalization (long-term surveillance). In the short-term surveillance period, postprocedural adverse events, signs of cholestasis, and need for repeated procedures are recorded. In the long-term surveillance period, participants are encouraged to contact the investigators if any symptoms of recurrent cholelithiasis are suspected. Participants will be contacted via phone or email 6 to 12 months later. Their health status will be evaluated using a questionnaire on the possible symptoms of choledocholithiasis (Multimedia Appendix 1). If any symptoms of possible gallstone disease are observed, the participant is invited for additional investigation (biochemical blood tests, transabdominal ultrasound, and MRCP on demand). All the enrollment, intervention, and surveillance procedures are listed in Multimedia Appendix 2.

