All imaging methods are somehow operator dependent (or assessor dependent). EUS can have higher operator dependency as agreed by experts in the field because it requires not only evaluation of images but also proper positioning of the scope [25]. On the other hand, EUS is considered to be able to detect smaller CBD stones, which increases its value. Overall, this potentially is reflected in meta-analyses when evaluating not common specificity or sensitivity but the range in different studies. For example, Meeralam et al presented a pooled sensitivity and specificity of 0.97 (range 0.91-0.99) and 0.90 (range 0.83-0.94) for EUS and 0.87 (range 0.80-0.93) and 0.92 (range 0.87-0.96) for MRCP, respectively [21].

In terms of the level of “invasiveness” of these diagnostic methods, MRCP can be considered the least invasive; however, it has its own disadvantages, such as possible reaction to the contrast material and contraindications for the procedure (claustrophobia and ferromagnetic foreign objects). Additionally, EUS can be compared to conventional upper endoscopy, and the main possible complication is injury of the gastrointestinal tract wall with the scope, which is extremely rare. However, this procedure requires sedation or general anesthesia. IOC could seem to be the most invasive option because it is performed during operation, but it is just an additional step in an already ongoing surgery.

Determination of the best exploration method greatly depends on local expertise and availability of certain procedures. At our institution, availability of magnetic resonance imaging is limited because of the lack of equipment, so we decided to choose investigational procedures performed by surgeons and endoscopists themselves to compare.

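### Secondary endpoint 1 counts true negatives, but on the procedures shown a symptom-free test-negative patient never has the duct examined again, so silent missed stones are scored as correct diagnoses

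*Protocol article*

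**What the plan says.** The Outcomes section lists diagnostic accuracy of the two strategies as the first secondary endpoint: "proportion of correctly diagnosed [true positive and true negative] cases in the entire sample; time frame: 6 to 12 months". Every patient therefore has to be classed as correctly or incorrectly diagnosed.

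The information for that classification comes from two sections.

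- **Procedure.** In the endoscopy-first arm, "If stones are seen in the extrahepatic bile ducts, ERCP and CBD stone removal are performed during the same general endotracheal anesthesia". In the cholecystectomy-first arm, ERCP likewise follows only when IOC finds stones.
- **Follow-Up.** During the inpatient stay after LC, "postprocedural adverse events, signs of cholestasis, and need for repeated procedures are recorded". After discharge, patients are asked to get in touch if symptoms arise. They are contacted by phone or email 6 to 12 months later: "Their health status will be evaluated using a questionnaire on the possible symptoms of choledocholithiasis". Blood tests, ultrasound and MRCP on demand depend on the answer: "If any symptoms of possible gallstone disease are observed, the participant is invited for additional investigation".

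The Introduction opens with "Gallbladder stones can be silent or symptomatic. This statement is also valid when speaking about choledocholithiasis". On duration, the Abstract says "Postoperative follow-up is 6 months". The Follow-Up section also sets surveillance at 6 months, with the contact made between months 6 and 12.

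**The concern.** Test-positive patients are verified by ERCP. Test-negative patients are verified by whether a missed stone makes itself known. A missed stone that stays silent leaves no trace in the data and enters the numerator as a true negative. The error runs one way: it can raise scored accuracy but never lower it.

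Accuracy is part of the aim stated in the Introduction. The Discussion adds that, if length of stay does not differ significantly, the other outcomes will be used to compare the strategies. A finding of similar accuracy could then carry weight although part of the similarity comes from how negatives are verified.

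The contact window adds a smaller problem. If a patient is classified from what is known at contact, one contacted at month 12 has had twice as long to reveal a missed stone as one contacted at month 6.

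**Working it through.** **The plan's own figure.** The documents give no figure for the accuracy endpoint. The only sample-size figure is for length of stay, and it reproduces: SD = √((2.5² + 2.8²)/2) = 2.654; d = (7.13 − 5.37)/2.654 = 0.663; a two-sided t test at 0.05 with power 0.80 needs 36.7, so 37 per group and 74 in total. This point does not touch it.

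**Inputs**

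- Prevalence p: 0.25 to 0.75, the limits of the intermediate-risk group (Introduction). These are individual risk thresholds, so a sample prevalence at either end is an extreme case.
- EUS sensitivity 0.97 and specificity 0.90: the pooled values cited in the Discussion.
- Sensitivity of the comparison test: **assumed** 0.85, because the documents give no IOC figure. Specificity is assumed to be 0.90 in both arms.
- Silent share s, the fraction of missed stones that none of the described checks brings to light: **assumed**, shown from 0.25 to 0.75.
- Patients per arm: 106/2 = 53 (Abstract).

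**Formulas**

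- True accuracy = p·Se + (1 − p)·Sp
- Scored accuracy = true accuracy + p·(1 − Se)·s
- With the same p, Sp and s in both arms, scored difference = p·(Se₁ − Se₂)·(1 − s)

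With equal silent shares, the part of the difference that is due to sensitivity shrinks by the factor 1 − s.

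**Worked case, p = 0.50 and s = 0.50**

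- Se 0.97: true 0.485 + 0.450 = 93.5%; inflation 0.5 × 0.03 × 0.5 = 0.75 points; scored 94.25%.
- Se 0.85: true 0.425 + 0.450 = 87.5%; inflation 0.5 × 0.15 × 0.5 = 3.75 points; scored 91.25%.
- Difference: 6.0 points true, 3.0 points scored.

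**Range (percentage points)**

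| p | s | Inflation, Se 0.97 | Inflation, Se 0.85 | True difference | Scored difference |
|---|---|---|---|---|---|
| 0.25 | 0.25 | 0.19 | 0.94 | 3.0 | 2.25 |
| 0.25 | 0.50 | 0.38 | 1.88 | 3.0 | 1.5 |
| 0.25 | 0.75 | 0.56 | 2.81 | 3.0 | 0.75 |
| 0.50 | 0.25 | 0.38 | 1.88 | 6.0 | 4.5 |
| 0.50 | 0.50 | 0.75 | 3.75 | 6.0 | 3.0 |
| 0.50 | 0.75 | 1.13 | 5.63 | 6.0 | 1.5 |
| 0.75 | 0.25 | 0.56 | 2.81 | 9.0 | 6.75 |
| 0.75 | 0.50 | 1.13 | 5.63 | 9.0 | 4.5 |
| 0.75 | 0.75 | 1.69 | 8.44 | 9.0 | 2.25 |

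If few missed stones are silent, little is lost: at p = 0.50 and s = 0.10, the 6.0 points become 6.0 × 0.9 = 5.4.

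**Direction**

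- Equal sensitivities and equal silent shares: both arms are inflated alike, and the between-arm distortion is zero.
- Equal sensitivities, unequal silent shares: a spurious difference appears. At p = 0.50, Se 0.85 in both arms and s of 0.25 versus 0.75, it is 0.5 × 0.15 × 0.5 = 3.75 points.
- Sensitivities 0.97 and 0.85: the better test is inflated more only if its missed stones are silent more than 0.15/0.03 = 5 times as often.

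**Apparent sensitivity.** Computed from scored data it is Se/(Se + (1 − Se)(1 − s)). A true 0.85 would read as 0.85/0.9625 = 0.88 at s = 0.25 and 0.85/0.8875 = 0.96 at s = 0.75.

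**Precision.** At p = 0.50, the standard error of the true accuracy difference is √((0.935 × 0.065 + 0.875 × 0.125)/53) = 5.7 points. Power for this contrast is about 18% with perfect verification, 9% at s = 0.50 and 5% at s = 0.75.

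**The case against.** The strongest objection is that the article nowhere states that absence of symptoms makes a true negative. A reference standard could be defined in the SAP or in Multimedia Appendix 2, neither of which is shown. That limits the conclusion to the procedures described. Within them, however, a definition cannot supply the status of ducts that were not examined; only an objective check of symptom-free negatives, which the article does not describe, would do that.

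The follow-up is also more than a questionnaire. Inpatient signs of cholestasis and self-reporting at any time can bring missed stones to light. Both lower the silent share, but nothing suggests that they bring it to zero.

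The effect is also small beside the sampling error. In the worked case, a 3.0-point loss compares with a standard error of 5.7 points, and the contrast has little power in any event. This limits the consequence, but a bias should still be declared in an endpoint named accuracy.

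A reader might go further in four ways that the documents do not support:

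- **That the scoring favours IOC.** This needs an IOC sensitivity below that of EUS. The article gives none; the 0.87 in the Discussion belongs to MRCP. The Discussion's IOC evidence points, if anything, the other way: one older trial found better predictive values for IOC than for EUS, and a systematic review found slightly higher sensitivity for IOC than for ERCP.
- **That the follow-up durations contradict each other.** The Abstract and the Follow-Up section both give 6 months; 6 to 12 months is the time of contact. Observation time varies between patients, but nothing shown makes it vary by arm.
- **That contact date shifts detection by a known amount.** No detection rate over time is given.
- **That missed stones cannot be confirmed because "availability of magnetic resonance imaging is limited because of the lack of equipment".** That statement explains the choice of tests to compare. MRCP on demand remains in the follow-up work-up.

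**Conclusion.** The point holds for secondary endpoint 1. On the procedures shown, the design cannot separate a true negative from a silent missed stone, and the endpoint as defined counts both as correct. Accuracy is inflated in each arm by p·(1 − Se)·s. Over prevalence 25% to 75% and silent share 25% to 75%, that is 0.2 to 1.7 points at sensitivity 0.97 and 0.9 to 8.4 points at an assumed 0.85. With similar silent shares, the less sensitive arm gains more, and half of any sensitivity-driven difference disappears if half of missed stones are silent.

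Which arm gains more, and by how much, is unknown, because both the IOC sensitivity and the silent share are assumptions here. The conclusion also presumes that the unseen appendix adds no objective check for symptom-free negatives. Length of stay and the sample size of 74 are unaffected.

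**What to change.** - Keep all randomised patients in the denominator, apart from those who withdraw and whose data the section Elimination From the Trial requires to be deleted. Splitting the endpoint into subgroups defined by test result would give up the randomised comparison.
- Rename the endpoint as accuracy against ERCP or clinical follow-up, and state how a negative is classified.
- Classify all patients over one common window and list later events separately. Since contact is made at 6 months or later, a 6-month window is available for everyone contacted, provided the date of symptom onset is recorded.
- Add a sensitivity analysis of accuracy over a stated range of silent-stone fractions, allowed to differ by arm.
- Report ERCP-confirmed positives and symptomatic retained stones by arm as descriptive components.
- Do not claim true sensitivity, negative predictive value or equal accuracy from this endpoint.

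The cost is a little more analysis and a less definite accuracy figure, with no added procedures or patients. As the trial is unblinded and 66 of 106 patients had been enrolled by June 2020, the change should be dated and recorded before accuracy is compared by arm.
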